# 1. BACKGROUND

Depression is costly for the individual and for the society world-wide and especially in established market-economy countries (World Health Organization, 2004). In monetary terms, the cost of depression due to treatments, reduced productivity and suicide has been estimated to amount to $83 billion for the year 2000 in the USA alone (Greenberg et al., 2003). This societal cost is only second to that of hypertension and is indeed far greater than that of other chronic conditions such as diabetes, heart disease or asthma (Druss et al., 2001).

Of note is the fact that the direct treatment costs account for only about 25% of the total societal cost of depression. As a matter of fact, the great majority of the cost of depression ($52 billion, or 62%) is incurred in the workplace as lost productive work time (Greenberg et al., 2003). Other researchers using different methodology have arrived at comparable estimates; for example, according to (Druss et al., 2001) cost of work loss among those who were treated for depression would be $11.5 billion for the whole USA in 1996. If all workers of depression, regardless of their treatment status, were counted, the sum went up to $44 billion in another study (Stewart et al., 2003). The estimates according to the National Comorbidity Survey Replication amounted to $36.6 billion (Kessler et al., 2006).

Of further note is the fact that the cost of depression in the workplace is not mainly due to absence from the job (absenteeism) but rather from reduced productivity while on the job (presenteeism). For example, the American Productivity Audit estimated hours lost due to depression among workers with major depression were 1.2 hours/week for absenteeism and 7.2 hours/week for presenteeism (Stewart et al., 2003). A newer survey revealed that depression was responsible for 8.7 days equivalent of absenteeism and 18.2 days equivalent of presenteeism per year per depressed employee (Kessler et al., 2006). Depression is indeed among the most costly of all health problems to employers (Wang et al., 2003). From a more holistic viewpoint, it is important to remember here that all this money counting has not yet taken into account the personal subjective sufferings of the afflicted and those of the family.

It is then no wonder then that several groups of researchers have sought for ways to reduce depression’s deleterious effects in the workplace. While a good number of controlled trials are reported in the literature that tried to reduce work-related stress in general through organizational, cognitive-behavioral and other interventions (Richardson and Rothstein, 2008; van der Klink et al., 2001), only two trials have examined work-related productivity loss. Rost et al (Rost et al., 2004) compared enhanced care against usual care for workers visiting twelve community primary care practices in USA. The enhanced care involved, in addition to the usual care by the primary care physicians, telephone contacts by care managers who reassessed the patients’ depressive symptoms, educated them about depression and its treatment, reported the patients’ status to the physicians and made recommendations for adjustment of treatment in accordance with the treatment guideline. Over two years, the intervention had some limited impact on depression (p=0.09) but significantly improved productivity by 6.1% (p<0.05) and tended to improve absenteeism by 22.8% (p=0.06). In monetary terms, the gain translated into $1491 for decreased presenteeism and $539 for absenteeism per one depressed employee per annum. These effects were more salient among consistently employed subjects.

Wang et al (Wang et al., 2007) examined a more aggressive outreach-treatment program in the workplace recently. They first screened employees from 16 large companies from diverse sectors and those who screened positive for possible depression were randomly allocated to usual care or intervention. Those assigned to usual care were informed that their responses indicated possible depression and advised to consult with a clinician. Those assigned to intervention received a systematic telephone intervention program, which assessed needs for treatment, facilitated entry into in-person treatment, monitored and supported treatment adherence and, for those who declined in-person treatment, provided a structured telephone psychotherapy. The intervention not only significantly reduced depression severity (p=0.001) but also increased effective hours worked (p=0.002) and job retention (p=0.02) through 12 months. The gain translated into 2 more hours per week, or 2 more weeks per year, than workers assigned to the usual care.

What we should not lose sight of in our fight against lost productivity in workplace is that minor depression or subthreshold depression, although less symptomatic than full major depression by definition, is still associated with substantial functional impairment (Judd et al., 2002; Wells et al., 1989) and as a matter of fact, due to its greater prevalence, may be responsible for twice as many disability days in toto than major depression per se (Broadhead et al., 1990). Moreover, minor depression may well be the most ominous harbinger to subsequent full-blown major depression (Judd et al., 1997).

Fortunately there is growing evidence that psychotherapies, especially cognitive-behavioral ones, may not only ameliorate subthreshold depression (Allart-van Dam et al., 2007; Cuijpers et al., 2007; Spek et al., 2007; Willemse et al., 2004) but also may prevent future major depressive episodes up to 18 months (Clarke et al., 1995; Clarke et al., 2001). On the other hand available evidence does not support effectiveness of pharmacotherapy for minor depression (Dimidjian et al., 2006; Paykel et al., 1988), except in the context of relapse prevention for recurrent depression (Geddes et al., 2003). In this randomized controlled study we therefore aimed:

1. To demonstrate the effectiveness of the CBT package for subtheshold depression in the workplace
2. To demonstrate the economic worthiness of this CBT package in the workplace

Correspondingly, the hypotheses addressed in this study include:

1. Whether the CBT package is significantly more effective than the usual EAP package in reducing the depression severity and preventing depression episodes among workers with subthreshold depression
2. Whether the CBT package can enhance work performance by at least $100 on average per worker per annum
   1. If all this is to be gained by increased work performance (greater effective hours worked), among 100 workers with an average hourly wage of $40, 10 must receive the package and gain 2 effective hours worked per month to compensate for $10000 per year.
   2. And if the CBT program prevents 0.1 person from resigning, this will mean a gain of $8000 per annum in terms of yearly wage, in addition to the educational and other costs that the company has poured into the workers.

The study will be a two-arm, parallel-group, TAU-controlled, non-blinded randomized study.

# 2. OBJECTIVES

## 2.1 Primary question

Our primary question is: “Among company employees with subthreshold depression, will a telephone-CBT program consisting of behavioral activation (BA) and cognitive restructuring (CR) in addition to the standard Employee Assistance Program (EAP) outperform EAP alone, in terms of depression severity (measured with BDI2) and work productivity (measured with HPQ) at the end of the program?”

The primary outcome measures in this study will therefore be:

1) depression severity at 4 months post-randomization as measured by the BD12

2) work performance at 4 months post-randomization as measured by the HPQ, which assesses “effective hours worked” for the past month

These two primary outcomes will be used to decide whether or not the intervention was effective.

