## 3.2. Sample size assumptions and estimates

A systematic review of psychological treatments, mostly CBT, for subthreshold depression yielded a Cohen’s d of 0.42 (95%CI: 0.23 to 0.60) at post-test and 0.16 (95%CI: 0.02 to 0.35) at 1-year follow-up (Cuijpers et al., 2007). ( a Cohen's d of .42 indicates a treatment effect (difference between control mean and intervention mean on the outcome measure) equal to 0.42 standard deviations (where standard deviation(SD) of interest if the SD of the outcome measure)

|  |  |  | 1:1 |  | If 1:2 |  | If 1:3 |  |
| --- | --- | --- | --- | --- | --- | --- | --- | --- |
| alpha | power | Effect size | n in each cell | Total N | n in active treatment | Total N | n in active treatment | Total N |
| 0.05 | 0.90 | 0.4 | **131** | 262 | **99** | 297 | **88** | 350 |
| 0.05 | 0.80 | 0.4 | **98** | 196 |  |  |  |  |

Thus, if we randomize 99 in the intervention group and twice that many in the control group (198) for a total of 297 randomized, we will have 90% power to detect a treatment effect assuming that this difference is equal to .40 standard deviations. However, these calculations ignore dropout. We expect that 90% will complete our month 4 followup, resulting in 89 respondents in the intervention group and 178 respondents at month 4 in the control group. In this situation, we will have 90% power to detect an effect size equal to .42 SD, which is exactly equal to our best estimate of what effect we expect to see at month 4 in this trial.

At month 15, we will have inadequate power to detect treatment effects since we expect those effects to be much smaller than those seen at month 4 (only about .16 SD's). However, in order to obtain insight into the next RCT to demonstrate prophylactic effect, we will conduct 15-month follow-up. Analyses of the 15-month follow-up will be exploratory.

If we think we can recruit 300 participants, we will go for 1:2 (intervention: control) allocation. If we expect to get closer to 200 total subjects only, we will go for 1:1 allocation, because the number in the active arm is important for journal reviewers and we would then not have 100 in the intervention group under 1:2 randomization.

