## 5.3. Assessment of response variables

### 5.3.2. Independence of the self-reports

Our primary outcome, the BDI2 to be completed by the participant, is mailed back confidentially to the CRC and not to the therapist, in order to assure anonymity and independence of the ratings.

It is explicitly explained in the letter that these data will not be shared with the counselor, so honest disclosure is most welcome.

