### 6.1.4. Analyses of Primary Outcomes

Our two primary outcomes are the BD12 measure of depression severity and the HPQ measure of effective hours worked, both assessed at the month 4 follow-up. Both of these measures are continuous/ordinal variables so will compute the mean BD12 and mean HPQ at month 4 in the two groups, control and intervention.

We will first do unadjusted analyses to compare the means using a t-test. We will then do several adjusted analyses. First will use ANCOVA to compare the month 4 means on the outcome adjusting for baseline differences on the outcome. ANCOVA is simply another term for regression. For example, in one model, BD12 at month 4 will be the outcome and treatment group (a 0/1 variable) and baseline BD12 will the independent variables. These ANCOVA analyses provide estimates of "adjusted" month 4 group means as well as estimates of the adjusted difference in the group means (along with a p-value and confidence interval for the difference).

We will also do adjusted analyses which control for additional baseline variables, including variables which differ significantly between the control and intervention groups and variables which are strong predictors of the outcome under analysis. We will compare the estimated difference in group means and p-values to those obtained from the unadjusted analysis and the ANCOVA analyses which adjusts only for the baseline value of the outcome.

These analyses will be restricted to subjects who complete the month 4 follow-up (all of the statistical methods described above drop from the analysis those with a missing value on the outcome). Since a true intent-to-treat analysis estimates treatment effects based on data from all randomized subjects, not just those who complete a given follow-up, we will also do some mixed-model hierarchical linear models (HLM) to estimate treatment effects based on all subjects. NOTE: If the response rate is high at the month 4 follow-up (say at least 90%), bias due to missing data will likely be quite small and these analyses may not be necessary.

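### Two primary outcomes decide effectiveness with no rule for combining them, and the stated 90% power covers only one outcome tested at 0.05

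*Protocol*

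**What the plan says.** Section 2.1 (Primary question) asks whether telephone CBT added to the EAP outperforms the EAP alone "in terms of depression severity (measured with BDI2) and work productivity (measured with HPQ) at the end of the program". It lists BDI2 and HPQ at 4 months as the two primary outcomes and adds: "These two primary outcomes will be used to decide whether or not the intervention was effective".

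Section 6.1.4 (Analyses of Primary Outcomes) repeats: "Our two primary outcomes are the BD12 measure of depression severity and the HPQ measure of effective hours worked". Both get the same series of analyses: t-test, ANCOVA on the baseline value, then further adjustment. No joint criterion, order of testing or division of alpha is given, and no significance level is stated there.

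Section 5.3.2 uses the singular: "Our primary outcome, the BDI2 to be completed by the participant, is mailed back confidentially to the CRC".

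Section 3.2 has one calculation, at alpha 0.05, with d = 0.40 before dropout and 0.42 after. Its effect size comes from one source: "A systematic review of psychological treatments, mostly CBT, for subthreshold depression yielded a Cohen’s d of 0.42 (95%CI: 0.23 to 0.60) at post-test". It concludes that, "for a total of 297 randomized, we will have 90% power to detect a treatment effect" of 0.40 SD. No expected effect or SD is given for HPQ.

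**The concern.** Two test results must yield one decision, and the protocol supports three ways of reaching it. The conjunction in the primary question points to requiring both. The two separately numbered aims and hypotheses in section 1 (depression, and economic worth) would fit separate claims. Section 5.3.2 points to BDI2 alone. The type I error and the power differ under each, and the power statement in section 3.2 matches only the last.

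A split result is realistic on the protocol's own evidence. Section 1 describes a primary-care trial of enhanced care in which depression gave p = 0.09 and productivity p < 0.05. The same pattern here would be a success under an either-rule and a failure under a both-rule or BDI2 alone. In a non-blinded trial the rule should not be left to be chosen once the results are known.

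**Working it through.** **Inputs from section 3.2.** Alpha 0.05; power 0.90; d = 0.40; allocation 1:2; 10% dropout, leaving 89 and 178; d = 0.42 after dropout.

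**Assumptions, because the protocol gives no figure.** The correlation ρ between the two test statistics (both signed so that benefit is positive) runs from 0 to 0.8. HPQ d is 0.42, 0.30 or 0.20. There is one test per outcome, using the normal approximation.

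**Step 1. Reproduce the plan.** At 1:2, n(active) = 1.5 × (1.960 + 1.282)² / 0.40² = 98.5, so 99 and 3 × 99 = 297, as stated. At 1:1 the two-sided formula gives 132 per arm (stated 131). A one-sided 0.05 would give 108, so the table is two-sided.

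After dropout the expected test statistic is d × √(89 × 178 / 267) = 7.703d. At d = 0.42 this is 3.235, and power = Φ(3.235 − 1.960) = 0.899. The stated 90% is right for one outcome at two-sided 0.05.

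**Step 2. Both required, each at 0.05.** Joint power is P(Z₁ > 1.96 and Z₂ > 1.96), bivariate normal with means 3.235 and 7.703 × d(HPQ):

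| HPQ d | HPQ power alone | ρ = 0 | ρ = 0.3 | ρ = 0.5 | ρ = 0.7 | ρ = 0.8 |
|---|---|---|---|---|---|---|
| 0.42 | 0.899 | 0.808 | 0.820 | 0.831 | 0.845 | 0.855 |
| 0.30 | 0.637 | 0.573 | 0.594 | 0.609 | 0.624 | 0.631 |
| 0.20 | 0.337 | 0.303 | 0.321 | 0.330 | 0.336 | 0.337 |

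Type I error needs no adjustment under this rule.

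**Step 3. Either is enough, each at an unadjusted 0.05.** With no effect on either outcome, the chance of at least one two-sided rejection is 1 − 0.95² = 0.0975 at ρ = 0. It is 0.095 at 0.3, 0.091 at 0.5, 0.083 at 0.7 and 0.078 at 0.8. Counting only false claims of benefit, 2.5% becomes 4.9% (ρ = 0) to 3.9% (ρ = 0.8).

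**Step 4. Either is enough, each at 0.025.** Error is controlled. Power per outcome at d = 0.42 is Φ(3.235 − 2.241) = 0.840. The chance of at least one success is 90–97% if both effects are 0.42, and 84–88% if HPQ d = 0.20.

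**Step 5. Size for 90% at d = 0.42, 1:2, 10% dropout.**
- Each outcome at 0.025: 106 + 212 = 318 analysed; 318 / 0.9 gives 354 randomised.
- Both required (ρ = 0, equal effects, so √0.90 = 0.949 power for each): 110 + 220 = 330 analysed; 330 / 0.9 gives 367 randomised.

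**Step 6. Effect of ANCOVA.** If baseline and month-4 scores correlate at r, the expected statistic is divided by √(1 − r²). The protocol gives no r. For illustration with ρ from 0 to 0.8: at r = 0.3, joint power is 85–89% if HPQ d = 0.42. At r = 0.5 it is 93–94% if HPQ d = 0.42, and 73–76% if HPQ d = 0.30.

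**The case against.** Much of the case on the other side is fair.

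- **Alpha allocation is often left to an SAP, which is not shown.** That stands for the detail. It does not cover a protocol that makes two outcomes decisive and gives a power figure matching one. An SAP cannot turn 297 randomised into 90% unadjusted joint power under a both-rule with the stated effect.
- **The primary question joins the outcomes with a conjunction.** The natural reading is that both are required, and then the error rate is sound and the fault is in the power. This stands, but sections 5.3.2 and 1 point elsewhere and no rule is written down.
- **A reader might infer that the false-positive rate is nearly doubled.** The documents do not support this as a general statement. It needs the either-reading and correlation near zero, and section 6.1.4 does not say that each outcome is tested at 0.05. That level is inferred from the sample-size table.
- **A reader might also infer that the only alternatives are an inflated error or lost power.** Step 4 shows otherwise: an either-rule at 0.025 each controls error and can keep 90% or more for at least one success. It does so only with an HPQ effect that the protocol does not state.
- **The joint power figures ignore ANCOVA.** Correct. Step 6 shows that a moderate baseline correlation could restore 90% if the effects are equal. The protocol gives no such correlation and does not say which of its several analyses carries the decision. The figures for HPQ d = 0.30 and 0.20 are assumptions, not predictions.
- **Section 3.2 is in SD units, so a detectable 0.42 SD applies to HPQ too.** True. What is missing is any reason to expect that effect on HPQ.

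**Conclusion.** The concern holds in limited form. The protocol's decision sentence uses two outcomes without a rule, and its 90% power belongs to one outcome at two-sided 0.05. The arithmetic in section 3.2 is correct for that one outcome.

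The consequence depends on the rule. If both are required, the error rate is controlled and unadjusted power falls from 90% to 81–85% with equal effects, and further if the HPQ effect is smaller. If either is enough without adjustment, the two-sided error is 7.8–9.75%. The correlation and HPQ effects behind these ranges are assumed, and baseline adjustment would raise the power figures by an unknown amount. It would be wrong to say that the trial has an inflated error rate or lacks power. What can be said is that neither property is fixed until the rule is.

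**What to change.** In sections 2.1 and 6.1.4, state one rule before any outcome data are seen, including what is concluded about effectiveness when only one outcome succeeds.

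One rule that keeps the 5% error and the stated 90% is a fixed sequence: BDI2 first at two-sided 0.05, then HPQ at 0.05 as confirmatory only if BDI2 is significant. It fits the singular wording of section 5.3.2. It still needs a sentence on what is concluded if BDI2 succeeds and HPQ does not. The chance of confirming HPQ under the sequence is the joint power in step 2, not 90%. Requiring both, or allowing either at an adjusted alpha, is equally acceptable if the power is restated.

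In section 3.2, say that the 90% applies to BDI2 alone (or to one outcome at 0.05), and give the power under the chosen rule with an explicit HPQ assumption. Bring section 5.3.2 into line with section 2.1.

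The cost is about a paragraph of text. Under the sequence, an HPQ effect without a BDI2 effect cannot be claimed as confirmatory, which is a real loss given the economic aim. Under the other rules the stated power becomes less favourable. Restoring 90% without relying on ANCOVA, under the assumptions of step 5, would take about 367 randomised for both-required, or 354 for 90% on each outcome at 0.025.

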## 2.2. Secondary questions

Secondary outcomes will include:

1. At 4 months post-randomization
   1. depression severity as measured by K6
   2. client satisfaction　[VAS for satisfaction with the company’s support for mental stress, and a detailed ad hoc questionnaire for those who received telephone CBT]
2. At 15 months post-randomization
   1. depression severity [BD12 and K6]
   2. work performance
      1. “Effective hours worked” for the past month [HPQ]
      2. Job retention: has the person quit his/her job by 15 months post-randomization [yes/no, if yes when did the participant quit the job? The latter information is important for survival analysis.]
   3. client satisfaction [VAS]
   4. use of EAP services, use of health services (physical or mental), suicidal attempt, hospitalization (physical or mental) [yes/no for 15 months post randomization]
   5. time to incident major or minor depressive episode during the 15 months post randomization

## 2.3. Subgroup hypotheses

The effectiveness of the program may differ according to the initial severity of depression. We will therefore use as one stratification factor high/low subthreshold depression, and analyze the results according to these a priori defined subgroups. Because we do not have enough sample size to have adequate power to detect if treatment effects vary significantly by subgroup (i.e. for subgroup hypotheses), these will be more exploratory (i.e. hypothesis generating) than definitive analyses. Although we will test for treatment by subgroup interactions, our focus will be descriptive, describing the pattern of treatment effects by subgroup. To reduce the number of these analyses, we will focus on our primary outcomes (BD12 and HPQ at month 4).

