### 3.1.1. Inclusion criteria

1. Age 20-57 at study entry [because the retirement age is usually 60, we have to recruit the patients well before 60 in order to allow time for follow-up]
2. Men and women
3. Currently employed full-time (either regular or temporary) by the business company
4. Expected to be employed full-time for 2 years after screening
5. K6 scores greater than or equal to 9 (or 10) at screening
6. BDI2 scores greater than or equal to 10 at 2^nd^ screening (CIDI interview)

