### 3.3.4. Intervention allocation

We will randomize eligible subjects to intervention and control groups at a ratio of 1:2. Randomization will be stratified on three variables, namely depression severity at baseline (BDI2=<19 vs >=20), absolute presenteeism prior to baseline (6 or higher vs 5 or lower, based on the obtained median of the eligible subjects in the pilot run) and center (Office X, Factory Y, Factory Z). Assuming that subjects are recruited from 3 sites, there will be a total of 12 strata. The study statistician will prepare 12 lists of random assignments ahead of time, one for each of the 12 strata. Each list will be blocked to ensure that the ratio of intervention to control is exactly 1:2 at set intervals within each stratum. The statistician will send these lists to the research assistant who is not involved in any other aspects of the study and who will build a spreadsheet that enables concealed sequential allocation and will be responsible for keeping these lists in the safe place.

Before randomizing an individual, the CRC will make a final determination of whether or not the person is eligible to be in the randomized trial. For example, prior to randomization, we will exclude those who score too low (BDI2=<9), which may well occur because of the difference between K6 and BDI2 and due to time elapsed for screening, because those who score too low at baseline will have less room for improvement. Once the CRC determines the eligibility of the participant, she will enter his/her registration number and the stratification variables to the spreadsheet which will automatically generate the allocation according to the pre-determined random sequence. The entered variables cannot be undone in order to guarantee allocation concealment.

Those randomized to control group will be put on a waiting list and after 15 months can receive the telephone CBT if they wish to do so.

One stratification factor is BDI2>=20 and BDI2<=19. This cutoff was chosen because our previous study suggests the score ranges 14-19 to be mildly ill, 20-28 to be moderately ill and 29- to be severely ill (Hiroe et al., 2005) and because our pilot study suggested that this is about the median BDI2 value for employees with K6>=9.

Another stratification factor is presenteeism, because this will be one of our primary outcomes and it is important to make sure that some effect can be seen, when in fact there is, probably among the more disturbed people.

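### The interaction with initial severity is tested only on BDI2 split at 20, which costs about a third or more of the information if the effect changes roughly linearly with baseline score

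*Protocol*

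**What the plan says.** Protocol section 2.3 opens with the hypothesis: "The effectiveness of the program may differ according to the initial severity of depression". It turns initial severity into a two-level factor and commits to "use as one stratification factor high/low subthreshold depression, and analyze the results according to these a priori defined subgroups". On the test, it says: "Although we will test for treatment by subgroup interactions, our focus will be descriptive, describing the pattern of treatment effects by subgroup". The outcomes are the two primary ones, BDI2 and HPQ at month 4. The section is open about the limits: "we do not have enough sample size to have adequate power to detect if treatment effects vary significantly by subgroup", and it calls the analyses hypothesis generating.

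Section 3.3.4 sets the cut at a baseline BDI2 of 19 or less versus 20 or more and gives two reasons. The first is clinical: a previous study placed 14-19 as mild, 20-28 as moderate and 29 upwards as severe. The second is that "our pilot study suggested that this is about the median BDI2 value for employees with K6>=9". The same factor is one of three that stratify the randomization. Section 3.1.1 requires "BDI2 scores greater than or equal to 10", so the score is truncated below.

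The primary-outcome analyses in section 6.1.4 use baseline BDI2 as a continuous score, but only as a covariate. No treatment-by-baseline term appears there. Presenteeism and center are stratification factors only, so the high/low split is the only effect-modification analysis planned.

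**The concern.** The question is about a graded quantity, and the protocol collects that quantity as a score. The test uses only which side of 20 a participant falls on. Scores of 10 and 19 count as the same severity, while 19 and 20 count as different. The four lowest eligible scores (10-13) are merged with the mild band, and the moderate band with the severe one.

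The protocol's own reasoning leans towards a gradient. Section 3.3.4 excludes scores of 9 or below because such people have little room to improve, and that argument does not obviously stop at 10.

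At stake is the precision of the one analysis that could suggest whether benefit depends on severity. The test is already admitted to be weak, so an avoidable loss of precision matters more. The form of the test is fixed in the protocol itself, so it has not simply been left open for a later analysis plan.

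**Working it through.** **Inputs from the protocol.** Cut at 20, said to be about the pilot median (3.3.4). Lower limit of 10 (3.1.1). Allocation 1:2 (3.3.4). Expected month-4 respondents 89 + 178 = 267, and expected effect 0.42 SD (3.2). The protocol gives no SD or shape for baseline BDI2 and no power figure for the interaction, so those are assumed below and shown as a range.

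**Step 1: the protocol's own figures.** With two-sided alpha 0.05 and power 0.90, (1.960 + 1.282)² = 10.51. At d = 0.40 and 1:2 allocation, the control group needs 3 × 10.51 / 0.16 = 197.0, rounded up to 198, with 99 in the intervention arm: 297 in total, as stated. With 89 + 178 and d = 0.42 the power is 89.9%, against 90% stated. These figures reproduce.

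**Step 2: information kept by a split.** If the treatment effect is linear in the modifier X, testing the interaction on the indicator of X ≥ c instead of X keeps a fraction r² = corr(X, 1[X ≥ c])² of the information. The standard error, on a comparable scale, is larger by 1/√r². For a normal X with a share p above the cut, r² = φ(q)²/(p(1 − p)), where φ is the standard normal density and q its quantile at 1 − p. At the median this is 2/π = 0.637: 36.3% lost, standard-error factor 1/√0.637 = 1.25.

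**Step 3: sensitivity to the assumed distribution.**

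| Assumed baseline BDI2 | r² kept | Lost | SE factor |
|---|---|---|---|
| Normal, cut at median | 0.637 | 36% | 1.25 |
| Normal, 40/60 | 0.622 | 38% | 1.27 |
| Normal, 30/70 | 0.576 | 42% | 1.32 |
| Normal truncated at 10, cut 20, 44-56% above the cut | 0.628-0.668 | 33-37% | 1.22-1.26 |
| Normal truncated at 10, cut 20, all means and SDs tried | 0.547-0.677 | 32-45% | 1.22-1.35 |
| Right-skewed (gamma from 10), median about 20 | 0.566-0.604 | 40-43% | 1.29-1.33 |
| Uniform 10-29 | 0.752 | 25% | 1.15 |

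The 45% end comes from a case with only 17% above the cut, which is well off the median.

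**Step 4: effect on power at 267 respondents.** With residual SD 1 and X in SD units, SE = 1/√(267 × 1/3 × 2/3) = 1/√59.33 = 0.130. Let g be the assumed change in effect, in outcome SDs, per SD of baseline BDI2. Power is Φ(g/SE − 1.96) for the score and Φ(0.798 g/SE − 1.96) for a median split, since √0.637 = 0.798.

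| g | Score | Split at median |
|---|---|---|
| 0.10 | 12% | 9% |
| 0.20 | 34% | 23% |
| 0.30 | 64% | 45% |
| 0.42 | 90% | 73% |

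Simulation at g = 0.30 gives 61% versus 43%, for both a normal and a truncated baseline score.

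**Step 5: the reverse case.** If the effect is a step at 20, the roles swap: the linear term keeps only r² of the information that the split has, which is 64% for a normal score cut at its median.

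**The case against.** The strongest case on the other side has four parts.

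- **The cut has reasons behind it.** It follows a published severity band, is fixed in advance and so cannot be chosen from the data, and is a blocked stratum, which keeps the arms near 1:2 within each subgroup. A reader might infer that the split brings nothing. Section 3.3.4 does not support that, and the descriptive table is worth keeping.
- **The limits are disclosed.** Section 2.3 says that power is inadequate, the analysis is exploratory and the focus is descriptive. Section 2.1 rests the decision on effectiveness on the two primary outcomes. This stands, and it keeps the point minor. It does not remove it: a weak exploratory test still gains from using the score, and an effect plotted across the baseline range is also descriptive.
- **The size of the loss is not known.** It would be tempting to say as a fact that more than a third of the information is thrown away. The protocol does not give the distribution. The pilot figure, "this is about the median BDI2 value for employees with K6>=9", describes people before those with low BDI2 and those with a current major depressive episode are removed. These exclusions push the median in opposite directions, so the position of the cut among randomized participants is uncertain.
- **The score is not always the more sensitive choice.** A step near 20 would favour the split, and the room-for-improvement argument could also point to a curve. With about 267 respondents, a check for non-linearity will itself be weak.

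The practical gain is also limited. At g = 0.20 power is low either way. At g = 0.30 the effect would run from 0.42 − 0.30 = 0.12 at one SD below the mean to 0.42 + 0.30 = 0.72 at one SD above, which is a strong interaction.

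**Conclusion.** The point holds in a conditional form. For a graded hypothesis, the protocol fixes a test that uses only two levels of a measured score. If the effect changes roughly linearly with baseline BDI2 and the cut lies near the median of a unimodal distribution, about a third or more of the information on the interaction is lost. The loss is 36% for a normal score, 32-45% across the unimodal shapes tried (the upper end with the cut off the median) and 25% for a uniform one. The interaction standard error is about 1.2 to 1.35 times larger for the unimodal shapes.

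Two stronger readings are not supported. The main result is not weakened: the ANCOVA in section 6.1.4 already uses baseline BDI2 as a continuous covariate. Nor does the document say that this analysis would decide who is offered the programme. Stratifying the randomization at 20 is not a fault. This is a low-severity improvement to an analysis that the protocol already presents as exploratory.

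**What to change.** Keep stratification at 20 and the descriptive high/low table. In section 2.3, state that the interaction will be tested with baseline BDI2 as a continuous score:

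- For month-4 BDI2, add a treatment × baseline BDI2 term to the ANCOVA in section 6.1.4.
- For month-4 HPQ, whose ANCOVA adjusts only for baseline HPQ, add both baseline BDI2 and its product with treatment.
- Check for non-linearity, and show the estimated treatment effect with its confidence interval across the observed baseline range.
- Keep the analysis labelled exploratory.

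The cost is a sentence or two of text and one or two model terms, with no new data or participants. The downside is reliance on an approximately linear trend. If the effect is truly a step at 20, the linear term is the less sensitive test, and the retained high/low table gives some view of that case.
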